#### Trial suspension criteria

Trial will be suspended if serious adverse events (SAEs) occurred during the trial.

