#### Participant withdrawal criteria

Participant will withdraw or be rejected for further participation if:
Voluntarily quittingPoor adherenceAny violation of the inclusion criteriaAllergic to two or more of the originally intended drugs or have other specific and intolerable adverse reactionsDrop-out or loss of follow-up during observationLater examination finds other serious diseases (serious heart and liver function damage, blood disease, etc.) or special physiological changes (pregnancy, etc.) and not fit to continue the study

The reasons for the excluded cases will be explained, and the case report form will be kept for future reference. Anyone withdrawn within two weeks after receiving treatment will not be included in the per-protocol population and analyzed as missing data.

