##### Serious adverse events (SAEs)

Events that could lead to any of the following outcomes are included in the serious adverse events (SAEs), which will be observed, monitored, and judged by researchers, and gave timely treatment and reported to relevant authorities.
Hospitalization or prolonged treatmentCripple or life-threatening complicationsFetal deformity or significant disability or death

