#### Treatment of acute-onset UTI during the treatment period

Conduct urine culture, antimicrobial susceptibility testing, and the colony count immediately, then give a sufficient amount of oral or parenteral antibiotics for 7–14 days. Acute-onset infections should be treated with culture-directed antibiotics according to patients’ existing antimicrobial susceptibility testing records at first. In other situations, antibiotics will be prescribed empirically while awaiting the result of urine culture.

Such cases mentioned above should be marked as no recovery (NR).

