### Safety evaluation

Safety evaluation will be performed at the time of the beginning and the end of the trial, including (1) blood routine, stool routine, and stool occult blood; (2) liver and kidney function; and (3) electrocardiogram. Keep in touch with the participants to keep abreast of adverse events or emergencies. The relationship between the experimental drugs and adverse events will be assessed with five grades of “positively related, possibly related, impossible to judge, possibly unrelated, and definitely unrelated” [21], so as to judge the adverse reactions and to count the incidence of it.

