### Quality control of data

We will strictly control the data quality from the following aspects:
Before the start of the trial, the experiment scheme was designed on the foundation of professional background knowledge and clinical experience of all participants and researchers, so as to ensure the scheme is scientific and operable.Patients will be selected in strict compliance with inclusion and exclusion criteria.The randomized, double-blind design will be followed throughout the experiment.Strictly follow the experimental protocol for treatment, testing, and evaluation of efficacy.Researchers, cases observers, investigators, and data entry personnel will be trained regularly to ensure that any observation and examination results in the test are recorded in the CRF in a true, accurate, complete, and timely manner. Each site will be visited termly by the trial monitor.The data in CRF will come from and be consistent with the original file. Alteration is forbidden to be made at will. Any correction shall be made by keeping the original record legible and signed by the person making the correction.Ensure the subject’s safety and record timely. If SAE occurs during the clinical trial, take appropriate treatment for the subject and report to the responsible person immediately.Statistical experts are involved in designing experiments and evaluating data until the end of the study.DMC is independent from the funder and has no competing interests with the study organizers.

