### Unblinding

Unblinding procedures are divided into two parts. The first unblinding will be performed after the data collection was complete. In this step, all data will be distinguished into two groups, without specifying which is the control or treatment group. After the statistical analysis is completed, the second unblinding will be conducted to uncover which is the control group or the treatment group. Emergency unblinding is permissible if necessary for safety reasons, such as SAEs that occurred during the trial. The reason and time of emergency unblinding will be documented and reported.

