## Trial status

This trial was registered at the Chinese Clinical Trial Registry (registration number: ChiCTR2100041914) in January 2021. Recruitment will begin in August 2021 and it is anticipated that enrollment will be completed in December 2023.

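### The suspension rule stops the whole trial whenever SAEs occur, whatever their cause, arm or number, and a severe UTI recurrence could trigger it

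*Protocol article*

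**What the plan says.** The protocol article has a one-sentence section, Trial suspension criteria: "Trial will be suspended if serious adverse events (SAEs) occurred during the trial". The section directly before it, Participant withdrawal criteria, deals with individuals ("Participant will withdraw or be rejected for further participation if") and has its own list of reasons.

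The section Serious adverse events (SAEs) sets the scope: "Events that could lead to any of the following outcomes are included in the serious adverse events (SAEs"). The first outcome listed is admission to hospital or lengthened treatment. Researchers are to observe, monitor and judge these events, treat the patient and report to the authorities.

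Elsewhere SAEs are handled patient by patient:

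- Quality control of data: "If SAE occurs during the clinical trial, take appropriate treatment for the subject and report to the responsible person immediately".
- Unblinding: "Emergency unblinding is permissible if necessary for safety reasons, such as SAEs that occurred during the trial".
- Safety evaluation grades causality: "The relationship between the experimental drugs and adverse events will be assessed with five grades of" relatedness, running from positively related to definitely unrelated.
- Safety indicators lists the incidence of SAEs as a quantity to be reported.

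For an acute infection during treatment, the article's instruction is to "give a sufficient amount of oral or parenteral antibiotics for 7–14 days" and to mark the case as no recovery. UTI recurrence is the primary outcome.

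**The concern.** The rule is mandatory and unconditional. An SAE in the placebo arm, or one unrelated to any study drug, triggers it just as a related one does. The five-grade causality scale, which is the natural filter, is not connected to it.

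The definition widens the trigger further. It counts events that could lead to admission or longer treatment, as well as those that did, and it exempts no study-outcome event. A recurrence severe enough for admission and parenteral antibiotics would qualify. The trial could then be halted by the event it exists to count.

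Two things are at stake. If the rule is followed, recruitment stops at all three centers and perhaps dosing too, and the article states no route to restart. If dosing stops, patients in mid-course have their TLF or placebo and their two-weekly antibiotic rotation broken, which adds noise to the recurrence comparison. If the rule is passed over when an unrelated SAE occurs, the trial breaches its own written safety rule.

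**Working it through.** **Reading the text**

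1. *Level of the rule.* Withdrawal of participants has a separate section, so the suspension section acts on the trial.
2. *Narrowing elsewhere.* The SAE section lets researchers judge events. Table 4 gives the Data Monitoring Committee advisory and risk-reporting roles, and the Steering Committee audit and progress review. Neither gives anyone the decision to suspend or a threshold for it.
3. *Consistency.* Treating, reporting, unblinding and counting SAEs can all coexist with a pause, so there is no contradiction. They do describe a trial expected to continue through SAEs, which fits poorly with an automatic stop.
4. *Foreseeability.* The Adverse events (AEs) section cites pulmonary, renal and hepatic toxicity for the antibiotic regimen that both arms receive for 12 weeks.

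**Planned size**

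The only design figure used is the total of 200 patients. The 91 per group in Sample size reproduces from the unpooled normal formula at one-sided 0.025:

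(0.91×0.09 + 0.73×0.27) × (1.960 + 1.282)² / 0.18² = 90.5, so 91.

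With 10% attrition, 91/0.9 = 101.1, so 102 per group against 100 stated. The difference does not affect this point.

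**Chance of triggering the rule**

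The document gives no SAE rate. Let r be an assumed per-patient risk of an SAE over the 24 weeks, independent between patients.

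- At least one: 1 − (1 − r)^200
- At least two: 1 − (1 − r)^200 − 200r(1 − r)^199

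| r (assumed) | Expected SAE patients (200r) | At least one | At least two |
|---|---|---|---|
| 0.1% | 0.2 | 18% | not computed |
| 0.25% | 0.5 | 39% | not computed |
| 0.5% | 1 | 63% | 26% |
| 1% | 2 | 87% | 60% |
| 2% | 4 | 98% | 91% |

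Break-even risks for at least one SAE:

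- 50% chance: 1 − 0.5^(1/200) = 0.35%
- 95% chance: 1 − 0.05^(1/200) = 1.49%

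Median patient number for the first SAE, ln(0.5)/ln(1 − r): about the 69th patient at 1% and about the 35th at 2%.

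**Patients caught by a pause**

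Trial status says: "Recruitment will begin in August 2021 and it is anticipated that enrollment will be completed in December 2023". From 1 August 2021 to 31 December 2023 is 126 weeks. Assuming even recruitment, 200/126 = 1.59 patients per week.

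- In the 12-week treatment period: 1.59 × 12 = about 19
- In the 24-week participation: 1.59 × 24 = about 38

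**The case against.** The strongest counter-argument is that this is one sentence in a condensed article. Thresholds, decision-makers and restart rules commonly sit in the full protocol, which is not shown. That holds for the missing restart procedure, which is not a defect in itself. It does not rescue the sentence, which states an unconditional rule.

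Second, the sentence may be loosely worded, since the other SAE provisions act on the individual patient. The separate heading makes the trial-level reading much the more natural one, but looseness is possible. In that case the wording still needs correcting.

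Third, the article classes an acute infection on treatment as an efficacy failure, and nowhere calls a recurrence an SAE. The population is uncomplicated, so admissions may be few. This is fair as to frequency. An efficacy classification is still not an exemption from SAE status, and the claim is only that a severe recurrence could trigger the rule.

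Fourth, the probabilities rest on assumed rates, and the plural may mean more than one event. Both points stand, which is why a range and the two-or-more figures are given.

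Finally, suspension is not termination, a cautious hold errs toward patient safety, and a blinded pause would affect both arms alike with no evident bias. This limits the consequence. It does not justify a trigger that ignores causality.

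**Conclusion.** The concern holds. As written, the rule makes an interruption more likely than not once the per-patient SAE risk exceeds about 0.35%, if one event suffices. The chance reaches 95% only from about 1.5%. If two events are needed, it is 26% at 0.5%, 60% at 1% and 91% at 2%. These figures depend wholly on the assumed rates; the textual finding does not.

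The consequence is disruption. About 19 patients would be in mid-treatment at a typical pause, assuming even recruitment, and their regimens would be broken only if dosing stops too. No analysis, sample size or outcome definition changes. It should be fixed because the correction is cheap, not because the primary result is in doubt.

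**What to change.** Replace the sentence under Trial suspension criteria with a rule along these lines:

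- Every SAE leads to patient-level action (treatment, reporting, emergency unblinding if needed) and prompt causality review using the five grades in Safety evaluation.
- The whole trial is suspended only when that review, with the ethics committee, finds a safety concern, such as related and unexpected SAEs or an imbalance between arms.
- Hospitalization for a study-outcome UTI is reported as an SAE but does not by itself suspend the trial.

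The exact threshold is for the sponsor and ethics committee to set.

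The cost is a wording change and the ethics committee approval that the Ethics approval section already requires for important modifications. It costs no data and no patients. The one downside is that suspension becomes less automatic and depends on the review being prompt.

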##### Adverse events (AEs)

Our group has engaged in the basic and clinical researches of TLF against rUTI since 2000s, and our published data demonstrated TLF is helpful to reduce the recurrence of rUTI and protect renal tubular function in the clinic [10–15]. Therefore, we are very confident that the patients treated with TLF will not have AEs. It is reported that CLAT has potential risks of pulmonary, renal, and hepatic toxicity, and may cause gastrointestinal disturbances and skin rash [1].

All adverse events (AEs) will be collected systematically by asking participants specifically every 2 weeks and be recorded in detail on the specific form throughout the study. All relevant AEs will be reported in trial publications in the end.

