### Blinding

This trial follows the double-blind design. The division of the groups in this study will be blinded to all participants, investigators, and statisticians. The placebo and TLF are the same in the appearance of the drug package. What’s more, the drug distribution will be conducted by a pharmacist who is not involved in the study.

To assess whether participants stayed masked or knew their assignment, we will use the direct questioning method at the end of follow-up, that is, design a question in the CRF to ask the subjects to guess which group they are assigned to and ask them to give the basis or reason of guess. Then calculate blinding index (BI) according to the guess result and the implementation of the blind method can be judged.

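### All adverse events are collected, but publication is promised only for undefined relevant ones and only adverse reactions are named for counting among non-serious events; the comparison of all AEs by arm should be stated

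*Protocol article*

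**What the plan says.** Under Adverse events (AEs), collection is complete: "All adverse events (AEs) will be collected systematically by asking participants specifically every 2 weeks", with details recorded throughout the study. The next sentence narrows what is published: "All relevant AEs will be reported in trial publications in the end". The article does not define *relevant*, or say who decides it or when. The same section states that "we are very confident that the patients treated with TLF will not have AEs", drawing this from earlier findings on recurrence and renal tubular function. It then lists toxicities of the background antibiotics.

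Under Safety evaluation: "The relationship between the experimental drugs and adverse events will be assessed with five grades". The purpose given is "so as to judge the adverse reactions and to count the incidence of it". The grades include one for events that cannot be judged, and the text does not say which grades make an event an adverse reaction.

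Safety indicators lists the incidence of serious adverse events together with ECG, blood, urine, stool, liver and renal tests. The incidence of all AEs is not on the list. Serious events are those "which will be observed, monitored, and judged by researchers".

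On blinding: "The division of the groups in this study will be blinded to all participants, investigators, and statisticians". Under Unblinding, the data are first split into two unlabelled groups, and the arms are named once the statistical analysis is finished. Emergency unblinding for safety reasons is allowed.

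**The concern.** Primary objective and study hypothesis makes safety part of the aim and fewer side effects part of the hypothesis; the Discussion repeats this. The AE comparison therefore has to support a claim about the treatment.

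This is an add-on trial. Every patient takes rotating antibiotics, and the article itself names gastrointestinal, skin, renal, hepatic and pulmonary risks for them. When an event occurs in a patient taking both TLF and CLAT, a clinician's opinion on cause can rarely tell which was responsible. Randomisation can, because CLAT is the same in both arms and a difference in all AEs is then attributable to adding TLF.

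For non-serious events the text promises something weaker: a count after a relatedness judgement, and publication after a relevance judgement. At stake is whether the published safety comparison rests on all recorded events or on a selection whose rule is not given.

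**Working it through.** **The text, step by step**

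1. Collected: all AEs, all participants, every two weeks (Adverse events (AEs)).
2. Counted without a causality filter: SAE incidence, with laboratory tests and ECG assessed in everyone (Safety indicators; Safety evaluation).
3. Counted after a causality filter: adverse reactions, with the qualifying grades not named (Safety evaluation).
4. Published: AEs considered relevant, term undefined (Adverse events (AEs)).
5. Not promised anywhere: the incidence of all non-serious AEs by randomised arm.

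Steps 1 and 4 stand in adjacent sentences, so the narrowing is stated text.

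**When selection could occur**

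Blinding and Data entry and management keep investigators, data staff and statisticians blinded. Relatedness graded under the blind therefore cannot knowingly favour one arm. Unblinding names the arms after the analysis, which is before publication. Nothing says that relevance must be decided before then. Selection with the arms known is thus not excluded, though it is not described either.

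**Illustration of a filter applied equally to both arms**

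The article gives no AE rate, so there is no figure to reproduce. Assumptions: 100 per arm (from Sample size), a two-sided 5% test (from Data analysis), assumed proportions p1 (control) and p2 (TLF) with any AE, and the same share f of patients with an event kept in each arm.

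- Filtered difference: f × (p2 − p1)
- With a = f·p1, b = f·p2 and m = (a + b)/2, SE0 = √[2m(1 − m)/100] and SE1 = √[a(1 − a)/100 + b(1 − b)/100]
- Power = Φ[(b − a − 1.96·SE0)/SE1]

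For 15% v 35%:

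- f = 1: m = 0.25, SE0 = 0.0612, SE1 = 0.0596; (0.20 − 1.96 × 0.0612)/0.0596 = 1.34; power 91%.
- f = 0.5: a = 0.075, b = 0.175, m = 0.125, SE0 = 0.0468, SE1 = 0.0462; (0.10 − 1.96 × 0.0468)/0.0462 = 0.18; power 57%.

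| Assumed rates | f = 1 | f = 0.75 | f = 0.5 | f = 0.25 |
|---|---|---|---|---|
| 15% v 35% | 20 points, 91% | 15 points, 78% | 10 points, 57% | 5 points, 31% |
| 20% v 40% | 20 points, 88% | 15 points, 72% | 10 points, 51% | 5 points, 27% |
| 15% v 30% | 15 points, 72% | 11 points, 57% | 7.5 points, 39% | 4 points, 21% |

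A filter with no bias between arms leaves the risk ratio unchanged but shrinks the risk difference and the chance of detecting it. The table assumes that excess events are dropped as often as background events. A filter that removed mainly unrelated events would cost less.

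**The case against.** Much of the case on the other side stands.

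- **Not everything is filtered.** SAE incidence and the laboratory and ECG assessments carry no causality condition. A reader might infer that only drug-related events count anywhere in the trial; that is wrong. The point concerns non-serious AEs. Even there, the text says that adverse reactions will be counted, not that other AEs will be left out.
- **Graders are blinded.** A reader might infer that a team expecting no harm from TLF will discount events in that arm. While the blind holds, graders do not know which patients those are. The confidence sentence is an expectation, not a grading rule.
- **The experimental drugs may include CLAT.** Safety evaluation uses the plural, and a hypothesis of fewer side effects than CLAT alone makes sense only if reactions to CLAT are counted. On that reading, a TLF event blamed on CLAT still counts in the TLF arm. The narrower reading, TLF or placebo only, is possible but not required.
- **Selection after unblinding is not stated.** It is possible under the Unblinding section, no more than that.
- **A reported difference of zero is not supported.** It would need a filter that removes only the excess in the TLF arm, and the blind works against that.
- **This is a condensed article.** Table layouts and definitions often sit in the full protocol or analysis plan. That would answer a complaint about a missing table. It does not answer a written sentence that restricts publication to an undefined subset, or a safety prediction resting on efficacy and renal-function data.

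**Conclusion.** The point holds in a limited form. For non-serious AEs, the article commits to publishing an undefined subset and names only a count made after a relatedness judgement with no cut-off. Since safety and fewer side effects belong to the objective and hypothesis, this is a worse answer than the randomised comparison of all AEs, for which the data are already collected.

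The documents do not show that harm from TLF will be hidden, that relevance will be judged with the arms known, or that the graders are biased. The size cannot be derived from the article, because it gives no AE rate. On the assumed rates above, an equal filter keeping half the events halves the difference and lowers power from 72–91% to 39–57%. Those figures illustrate the direction of the loss and do not estimate it. The conclusion rests on the wording and does not depend on them.

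**What to change.** 1. In Adverse events (AEs), replace the publication sentence with a commitment to report all AEs and SAEs by randomised arm, regardless of judged relatedness, with risk differences and 95% confidence intervals.
2. In Safety evaluation, keep the five-grade assessment and the adverse-reaction incidence as a secondary table. State which grades count, including how events that cannot be judged are handled, and that grading is completed before any unblinding.
3. Delete the sentence predicting no AEs with TLF. The support given for it is evidence on efficacy and renal function, not AE data.

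The cost is a change of wording and one further table from data already collected every two weeks. The downside is a longer AE table and possibly a less favourable safety statement.

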##### Serious adverse events (SAEs)

Events that could lead to any of the following outcomes are included in the serious adverse events (SAEs), which will be observed, monitored, and judged by researchers, and gave timely treatment and reported to relevant authorities.
Hospitalization or prolonged treatmentCripple or life-threatening complicationsFetal deformity or significant disability or death

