### Screening and recruitment of participants

This study intends to enroll 200 cases mainly from the nephrology outpatient and inpatient departments, including 80 cases from Shanghai Municipal Hospital of Traditional Chinese Medicine, 60 cases from the Sixth People’s Hospital affiliated to Shanghai Jiaotong University, and 60 cases from Baoshan Hospital of Integrative Chinese and Western Medicine Affiliated to Shanghai University of Traditional Chinese Medicine. According to the inclusion and exclusion criteria set based on diagnostic criteria for rUTI and TCM syndrome differentiation, rUTI patients diagnosed with the qi-yin of spleen and kidney deficiency, damp-heat adhesion syndrome by TCM, will be considered as potential participants.

We have taken several methods to ensure recruiting enough participants to reach the target sample size. These methods are shown as follows:
We have counted the outpatient visits of the Nephrology Departments (sub-centers) of these three hospitals over the past three years in advance. And the statistical results showed that the annual outpatient visits of each Nephrology Department in each hospital exceed 60,000 per year. Therefore, each sub-center has enough rUTI patients to support the progress of this study.In order to recruit enough suitable subjects in time, we put recruitment advertisements in all three sub-centers.In order to avoid case shedding during observation and follow-up, we have special investigators responsible for contacting the subjects regularly and reminding and helping them to complete the detection and follow-up on time.

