## Outcomes

### Primary efficacy outcome

The primary efficacy outcome will be the recurrence rate at the 12th week of the follow-up period.

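### The SAE definition turns on possible outcomes and an undefined prolonged treatment, so UTI recurrences can be classed as SAEs and SAE incidence may be confounded with efficacy to an unknown degree

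*Protocol article*

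**What the plan says.** Under Serious adverse events (SAEs), the protocol article states: "Events that could lead to any of the following outcomes are included in the serious adverse events (SAEs". The first outcome on the list is hospitalisation or prolonged treatment; no length is given for the latter. Classification is left to judgement: these are events "which will be observed, monitored, and judged by researchers".

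Under Treatment of acute-onset UTI during the treatment period, the investigator is to take cultures and "then give a sufficient amount of oral or parenteral antibiotics for 7–14 days". The section gives such an episode one code: "Such cases mentioned above should be marked as no recovery (NR". That is an efficacy category from Table 3. The section does not mention AE or SAE status.

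Under Primary efficacy outcome: "The primary efficacy outcome will be the recurrence rate at the 12th week of the follow-up period". Statistics of recurrence counts recurrences from treatment to the end of follow-up. Safety indicators lists the incidence of SAEs.

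Other safety provisions exist. Under Adverse events (AEs): "All adverse events (AEs) will be collected systematically by asking participants specifically every 2 weeks". Safety evaluation grades the relation of adverse events to the experimental drugs on five levels and counts adverse reactions.

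Two procedures depend on SAE status. Trial suspension criteria ties suspension of the trial to SAEs, and Unblinding says: "Emergency unblinding is permissible if necessary for safety reasons, such as SAEs that occurred during the trial".

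**The concern.** A safety count should not move merely because a treatment works. Here two features of the definition let it do so. Seriousness depends on what might follow from an event, not on what did follow. And prolonged treatment stands where one would expect prolongation of a hospital stay, a criterion with practical use in a trial that recruits "mainly from the nephrology outpatient and inpatient departments".

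A UTI that may need parenteral antibiotics is easily regarded as an event that might end in admission. This holds whether or not a 7–14 day course is called prolonged. Such an episode can then be counted both as an efficacy failure and in SAE incidence.

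If the Tailin formulation (TLF) prevents recurrences, its arm would show fewer SAEs for that reason alone, and a real excess of harm on TLF could be diluted or hidden. With three centres and no rule on where possibility begins, the share of recurrences so classed could also differ between centres.

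**Working it through.** **1. The planning figures.** Sample size gives effective rates of 0.91 and 0.73, 90% power, significance level 0.025 and 91 per group. With unpooled variance and a one-sided 0.025 level:

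n = (1.960 + 1.282)² × (0.91×0.09 + 0.73×0.27) / 0.18² = 10.507 × 0.2790 / 0.0324 = 90.5, so 91.

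The stated figure reproduces. This confirms which proportions were planned; it says nothing about SAEs.

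**2. Assumptions for the illustration.** The article states no recurrence rate. I use the complements of the effective rates: 1 − 0.91 = 0.09 on TLF and 1 − 0.73 = 0.27 on placebo, with 100 patients per arm (the recruitment target). Let f be the share of recurrences classed as SAEs. The article does not fix f, so the full range from 0 to 1 is shown. UTI events add 9f v 27f SAEs. For masking, I add a hypothetical true harm of 9 v 1 SAEs, in patients other than those with recurrences. By itself 9 v 1 gives Fisher P=0.018.

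**3. Results** (expected counts, rounded; TLF v placebo; two-sided Fisher exact test, 100 per arm):

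| f | UTI events added | Harm 9 v 1 plus UTI events | P for the mixture |
|---|---|---|---|
| 0 | 0 v 0 | 9 v 1 | 0.018 |
| 0.10 | about 1 v 3 | about 10 v 4 | 0.16 |
| 0.25 | about 2 v 7 | about 11 v 8 | 0.63 |
| 0.50 | 4.5 v 13.5 | 13–14 v 14–15 | 0.8 or more |
| 1 | 9 v 27 | 18 v 28 | 0.13 |

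At f=1 the UTI events alone (9 v 27) give P=0.0015 in favour of TLF with no difference in harm.

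**4. Where the direction turns.** The mixture favours TLF when 9 + 9f < 1 + 27f, that is 8 < 18f, or f > 0.44. Below that the harm still points the right way, but from f=0.10 it is no longer significant.

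**5. No difference in true harm.** Let each arm have a 1% risk h of a true-harm SAE. The SAE risk is 1 − (1 − h)(1 − f×r), with r = 0.09 or 0.27. Per 100 patients this gives 1.0 v 1.0 at f=0, 1.9 v 3.7 at f=0.10, 3.2 v 7.7 at f=0.25, 5.5 v 14.4 at f=0.5 and 9.9 v 27.7 at f=1. The approximate chance of a significant SAE difference (normal approximation, two-sided 0.05, rough at low counts) is 0.12, 0.28, 0.56 and 0.90 for f = 0.10, 0.25, 0.5 and 1. With h at 5% and f=1 the risks are 13.6 v 30.6 and the chance is 0.84.

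**The case against.** A reader might infer that every treated recurrence counts as an SAE, and that the SAE comparison therefore measures efficacy instead of harm. The documents do not support either statement.

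- Classification is by researchers' judgement, not automatic. The acute-UTI section codes these cases only as no recovery.
- A 7–14 day course is the protocol's ordinary management. The Intervention section itself takes 14 days of sensitive antibiotics as the normal course for an acute episode. Nothing calls it prolonged.
- Coming straight after hospitalisation, prolonged treatment may be loose English for a prolonged stay. On that reading much of the overlap goes.
- All AEs are collected every two weeks, and causality is graded. A recurrence judged unrelated would not enter the count of adverse reactions, and a TLF harm judged related would.
- Unblinding is conditional on safety need; the SAE label alone does not make a patient eligible.
- The acute-UTI section covers only the treatment period, so the share of recurrences it governs is unknown.
- The article is condensed. An exemption for recurrences may stand in the full protocol, and its absence here is not a fault.

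These points defeat the categorical reading. The narrower one stands, because it rests on wording the article does state. Even if prolonged treatment means a prolonged stay, an event that might lead to hospitalisation still qualifies. Judgement without a rule is what leaves f open. AE collection and causality grading limit the problem, but the listed SAE incidence is not restricted to related events, so they do not remove it.

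**Conclusion.** The point holds as an ambiguity with a known direction and an unknown size. UTI recurrences can be classed as SAEs under the stated definition, and SAE incidence may then be confounded with the efficacy outcome in favour of the arm with fewer recurrences.

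The size depends wholly on f: there is no contamination at f=0, and UTI events dominate at f=1. Two assumptions carry the figures. The 9% v 27% are complements of an effective rate, not stated recurrence rates, and the 9 v 1 harm is hypothetical. Under them a small share is enough to take a harm signal out of significance, but reversing its direction needs more than about 44% of recurrences to be classed as SAEs. The wording should be corrected; the case does not show that the safety comparison is void.

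**What to change.** In the SAE section:

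1. Define an SAE as an event that results in a listed outcome.
2. Replace prolonged treatment with prolongation of an existing hospital stay.
3. State that a recurrence meeting the protocol's own definition is recorded as an efficacy event, and is an SAE only if it itself results in a listed outcome.
4. Report SAE incidence by arm with and without UTI events.

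The sections on trial suspension, SAEs, treatment of acute-onset UTI and unblinding should be reconciled on how recurrences are handled; what the suspension and unblinding rules should be is for the sponsor and investigators.

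The cost is a change of wording in the protocol and CRF and one more row in the safety table. The small downside is that fewer events would be reported in expedited form. Recurrences that do result in hospitalisation remain SAEs.
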